# Collaborative care model versus usual care for people with musculoskeletal conditions and co-existing anxiety and depression: protocol for a feasibility mixed-methods randomised controlled trial

**DOI:** 10.1192/bjo.2023.80

**Published:** 2023-06-15

**Keywords:** Anxiety disorders, collaborative care model, depressive disorders, musculoskeletal diseases, out-patient therapies

## Abstract

**Background:**

In the UK 17.8 million people have musculoskeletal pathophysiology, which becomes universal with age. Levels of discomfort and incapability correlate with symptoms of anxiety and depression. People with sufficient symptoms who seek care can benefit from collaborative diagnosis and treatment of mental and physical health organised by a case manager. This paper presents the protocol for a feasibility trial of collaborative care in an orthopaedic setting.

**Aims:**

To determine the feasibility and acceptability of providing collaborative care for patients with musculoskeletal conditions and co-existing symptoms of anxiety and depression identified on a screening tool in a physical and occupational therapy out-patient setting.

**Method:**

A two-arm parallel-group randomised controlled trial will recruit 40 adult out-patients with at least moderate anxiety and depression, who have been referred for physiotherapy and occupational therapy. Participants will be allocated on a 1:1 ratio to collaborative care or to usual care. Co-primary outcomes will be key feasibility indicators collected at baseline and at 6 months. A qualitative study will be conducted post-intervention to explore the acceptability and potential improvements to the collaborative care model.

**Results:**

This study will investigate the use of the collaborative care model for patients with musculoskeletal and co-existing moderate or severe levels of anxiety or depression.

**Conclusions:**

The results will provide important evidence to determine a future trial.

Musculoskeletal conditions are the leading cause of disability worldwide, affecting 1.71 billion people according to the World Health Organization.^1^ In the UK alone, 17.8 million people are currently diagnosed with musculoskeletal conditions,^2^ one in five adults consult their general practitioner (GP) for musculoskeletal symptoms each year^3^ and these problems are associated with approximately 30.8 million working days lost to sickness-related absence.^2^ Musculoskeletal conditions have a bidirectional relationship with aspects of mental and social health, substantially affecting quality of life, functioning and ability to engage in social roles.^3–5^

In the UK, one in six adults meets the criteria for a mental health condition.^6^ Despite the high prevalence, mental health conditions are often unrecognised in physical healthcare settings.^7^ There are numerous reasons for this, including the stigma associated with mental illness and the symptoms of the disorders themselves.^8^ Mental health conditions such as anxiety and depression that co-occur with physical health conditions are associated with health challenges for the individual and increased utilisation of healthcare services.^5^

People with co-occurring musculoskeletal conditions and symptoms such as anxiety and depression report higher pain intensity, lower quality of life and greater work absence.^3^ Depression in people with rheumatoid arthritis has been found to increase disability and reduce physical activity and concordance with treatment recommendations.^4^ In people with osteoarthritis, anxiety and depression negatively affect all domains of quality of life.^5^ Multiple studies have suggested that adequate treatment and support for anxiety and depression may therefore improve clinical outcomes for this patient population and also reduce the financial burden that these symptoms impose on healthcare services.^4,5^

A possible way to identify and improve clinical outcomes for people with both musculoskeletal problems and anxiety and depression is by implementing collaborative care.^9^ The ‘collaborative care model’ (CCM) was initially developed in the 1990s in the USA to facilitate multidisciplinary working between physicians, psychiatrists and clinical care coordinators,^9,10^ and it has since generated worldwide interest for its clinical and cost-effectiveness.^10^ Collaborative care involves care from three professionals: a physical healthcare provider (physiotherapist or occupational therapist), a mental healthcare provider (psychologist or psychiatrist) and a case manager who works closely with the patient to identify the mental and physical health support necessary.^10–12^ This model brings a more personalised approach to the care provided.^10^

Liaison psychiatry also has an important role to play in hospital settings in assessing and managing co-occurring mental disorders. However, in most cases, it operates on a ‘referral-and-triage’ (i.e. a reactive) approach. Collaborative care is a proactive approach that rests on screening and case identification. Collaborative care has been shown to enhance provision of liaison psychiatry in specialist settings such as renal care.^9^ The two approaches have been described by Curth et al,^11^ who are conducting a randomised controlled trial (RCT) to compare them.

Although collaborative care is not routine clinical practice in the UK,^10^ the National Institute for Health and Care Excellence (NICE)^12^ already recommends it for people with moderate to severe depression comorbid with cancer and diabetes.^13,14^ The CCM has never been tested in people with co-existing musculoskeletal and mental health symptoms, although evidence from a trial in people with chronic pain suggests that it may improve both disability and mental health outcomes.^15^ Before a definitive multicentre RCT can be recommended to determine the effectiveness of the intervention in a population with musculoskeletal conditions, there is a need to test the feasibility and acceptability of delivering the model within an orthopaedic setting. This paper describes the protocol for a trial in such a setting.

## Aims

The study will aim to determine the feasibility and acceptability of conducting a future multicentre trial comparing the collaborative care model (CCM) with usual care for people with musculoskeletal conditions and co-existing moderate or severe levels of anxiety or depression.

## Primary and secondary outcomes

The primary end-point will be the feasibility of the trial, which will inform a future power calculation. Therefore, co-primary outcomes are:
participation (number of patients willing to consent)recruitment (number of participants who consented)retention rates and adherence to the intervention.

Secondary outcomes are based on recommendations for testing an intervention while gathering information on its potential for implementation in a real-world situation:^16^
acceptability of self-reported outcome measures (completion rates, missing data)engagement with the CCM interventionto establish whether usage of additional healthcare resources can be estimated by participant self-reportto explore qualitatively the acceptability of the CCM intervention for patients and staff, including barriers and facilitators to implementationto estimate the staff costs required to deliver the intervention.

## Method

This will be a mixed-methods, unmasked (unblinded), parallel-group RCT. This protocol was written with reference to the Standard Protocol Items: Recommendations for Interventional Trials (SPIRIT) checklist.^16^

### Study setting

This will be a single-centre study in the UK, based in the Therapies Department of a tertiary National Health Service (NHS) orthopaedic hospital within the Royal National Orthopaedic Hospital (RNOH) NHS.

### Eligibility criteria

Inclusion:
patients over 18 years old, with a musculoskeletal problem and opting for a therapy out-patient appointmentscoring ≥20 on the Patient Health Questionnaire Anxiety and Depression Scale (PHQ-ADS)^17^able to provide written informed consent and willing to participateable and willing to complete questionnaires and study assessments.

Exclusion:
patients with a diagnosed mental health condition who are already receiving psychological treatment or are under the care of a specialist mental health servicescoring <20 on the PHQ-ADSlacking the capacity to consentunable or unwilling to complete questionnaires and study assessments.

### Interventions

#### Collaborative care model – intervention arm

The CCM involves three professionals: a physical healthcare provider (physiotherapist or occupational therapist), a mental healthcare provider (psychologist or psychiatrist) and a case manager working closely with the participant. In this trial, the case manager will work with the participant to screen, identify, coordinate and target mental health support according to their individual needs. This will involve:
developing a personalised care plancoordinating appointments with a psychologist or psychiatrist, if requiredmonitoring monthly progress using validated questionnaires first administered at baselineadjusting support needs accordinglycoordination of hospital appointments to reduce missed appointments and burden to the participantstreamlining communication between physical and mental healthcare professionals via email or internal referralsprovision of case manager care alongside routine physiotherapy or occupational therapy (usual care).

Participants will continue to be seen by a physiotherapist or occupational therapist as usual. Even if the participant is not seen again by the musculoskeletal specialist after a single visit, the case manager remains involved in the patient's care. The case manager can alert the musculoskeletal specialist to deterioration or lack of improvement in the participant's musculoskeletal condition, as well as refer participants for psychological or psychiatric support that provides more responsive input.

Participants who are randomised to the intervention group will be notified at the beginning of the trial that they will have a case manager only for the duration of the study. This will be clearly outlined during the consent process.

#### Usual care – control group

A physiotherapist, occupational therapist or both will assess the participants’ needs to help them work towards individualised goals that are important to them. These professionals will also inform, educate and empower participants to self-manage their physical capacity where possible. Following this initial assessment, participants will have a plan outlining their subsequent therapy, and exercises will be progressed as appropriate. Therapy will most often involve one-to-one sessions, but there may be instances where the participant will be involved in group classes. Physical therapy involves exercises and education; occupational therapy focuses on practical strategies to perform daily tasks. If the therapist identifies a need for additional mental health support, this will be requested via the GP or via an internal referral to the mental health services within the RNOH Trust, as per usual care.

### Outcomes

#### Feasibility outcomes

Feasibility will be assessed by collecting data on recruitment, retention and engagement in treatment. The following key feasibility indicators will be recorded:
number of patients excluded from participationproportion of eligible patients who agree to participateretention rates following randomisation and at follow-up time pointsengagement with first and follow-up appointmentscompletion of outcome data and rates of missing data.

### Secondary outcomes

#### Demographic data

Age, gender, ethnicity, marital status, highest qualification level and employment status will be collected at baseline.

#### Concomitant healthcare

Concomitant healthcare access for mental and musculoskeletal conditions that was not scheduled will be collected at 6 months from all participants (examples include GP appointments, specialist visits, accident and emergency department visits and other types of support, e.g. chiropractor or osteopath).

#### Patient-reported outcomes

All the study questionnaires have been validated and are widely used in both clinical and research contexts. Permissions have been obtained from copyright holders.

##### Anxiety and depression

We will use the 16-item Patient Health Questionnaire Anxiety and Depression Scale^17^ (PHQ-ADS) to measure the severity of anxiety and depressive symptoms. The reliability and validity of the PHQ-ADS have been established in adult populations.^17^

##### Quality of life

The three-level version of the five-item EuroQol-5 Dimension^18^ (EQ-5D-3L) is a standardised generic measure of health-related quality of life that is suitable for use in people with a wide range of health conditions and is recommended by NICE^12^ for economic evaluations in clinical trials. It can be completed by patients and may be used as a postal questionnaire or in an interview.

##### Physical health quality

The 14-item Musculoskeletal Health Questionnaire (MSK-HQ)^19^ assesses several domains: pain severity, physical function, work interference, social interference, sleep, fatigue, emotional health, physical activity, independence, understanding, confidence to self-manage and overall impact.

##### Level of pain

We will collect two measures of overall pain, the 11-point Numerical Pain Rating Scale^20^ (NPRS) and the Pain Disability Index^21^ (PDI). The PDI is designed to measure the degree to which aspects of patients’ lives are disrupted by chronic pain. The PDI rates seven categories of life activity on a scale from 0 (no disability) to 10 (activity is totally disrupted or prevented by pain).

##### Global change

The 15-item Global Rating of Change (GRoC) scale^22^ can indicate whether a person's overall health/condition is improving or worsening, as well as indicate the extent of this change.

### Participant timeline

All participants will be in the trial for 6 months. Fig. 1 shows the recruitment and flow of participants through the study.

**Fig. 1 fig01:**
[figure not shown]
Flow diagram for the trial. MSK, musculoskeletal; PHQ-ADS, Patient Health Questionnaire Anxiety and Depression Scale.

### Sample size

As this study is a feasibility trial, all analyses will be descriptive, with no hypothesis testing. Consequently, no formal sample size calculation has been conducted. We aim to recruit 40 patients in total, with 20 randomised to each arm.

The study aims to recruit these patients over 3 months, with a target recruitment rate of 20% of all eligible patients. It is estimated that there may be at least 200 new eligible patients in 3 months. Assuming this number of eligible patients, the recruitment rate could be estimated within ±6% with a 95% confidence level.

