### Screening and enrolment

Written informed consent will be obtained from all patients who agree to participate in the trial. This will be obtained during routine musculoskeletal appointments within 3 weeks after first being approached. After obtaining informed consent the research team will complete a screening process with the participant to ensure they meet the study inclusion and exclusion criteria. This will include asking them to fill in the PHQ-ADS questionnaire. If excluded from the trial, the participant will be informed of the reason.

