#### Quantitative data

Owing to the exploratory nature of this feasibility study, the sample size will be based on the pragmatic limits of recruitment. Since the primary aim of this study is to determine the feasibility of conducting a future RCT, a descriptive analysis will be performed to examine key feasibility and process-related outcomes. All quantitative data will be uploaded into SPSS^27^ for analysis, where recruitment, retention and follow-up rates at study completion will be quantified using absolute and relative frequencies and percentages of the overall population.

In particular, the percentage of potential participants who agree to undergo the screening assessment out of the total number of potential participants who were initially invited will be calculated. The percentage of the total number of participants who were enrolled into the study out of the total number invited will be calculated with a 95% confidence interval ±6%.

The main analysis will estimate the percentage of potentially eligible participants, consent and overall uptake. The retention, follow-up and outcomes rates will be calculated in relation to the number recruited. Engagement with the intervention will be described by the percentage of appointments attended as a proportion of booked appointments. An estimated engagement rate of approximately 90% (32/36 retained patients) will give a 95% confidence interval width of ±10%. Additional healthcare resources will be described by type and frequency of use in absolute numbers.

The means and confidence intervals of clinical outcomes will be calculated to determine their sensitivity to change. This will guide the identification of a primary outcome measure for a future RCT. In addition, we will determine the acceptability of the clinical outcomes by calculating percentage rates of completion for the PHQ-ADS, EQ-5D-3L, NPRS, PDI, MSK-HQ and the GRoC.

A detailed statistical analysis plan will be developed by the study statistician. To illustrate participant flow, we will report results using a CONSORT flow diagram.^23^

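### The 20%-of-eligible recruitment target needs a denominator the trial does not observe, and the analysis applies its ±6% to a different ratio

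*Protocol article*

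**What the plan says.** All references are to the Protocol article.

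- **Eligibility criteria:** a PHQ-ADS score of 20 or more is required, and a lower score excludes.
- **Screening and enrolment:** the order of events is explicit: "After obtaining informed consent the research team will complete a screening process with the participant to ensure they meet the study inclusion and exclusion criteria". The PHQ-ADS is part of that step.
- **Recruitment:** patients who decline may give a reason and, with permission, demographic data. No PHQ-ADS score is sought from them.
- **Sample size:** "We aim to recruit 40 patients in total, with 20 randomised to each arm". Recruitment is planned "with a target recruitment rate of 20% of all eligible patients", and "It is estimated that there may be at least 200 new eligible patients in 3 months". On that number, "the recruitment rate could be estimated within ±6% with a 95% confidence level".
- **Feasibility outcomes:** one key indicator is the share of eligible patients who agree to take part. The number excluded is also recorded.
- **Quantitative data:** the rate to be analysed is those enrolled "out of the total number invited will be calculated with a 95% confidence interval ±6"%. The share of invited patients who agree to be screened is also reported.
- **Primary and secondary outcomes:** the co-primary outcomes participation and recruitment are defined as numbers of patients, not as rates.

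**The concern.** Both the Sample size target and the Feasibility outcomes indicator divide by eligible patients. Under the described procedures, eligibility on the PHQ-ADS is known only for people who have already consented. Among patients known to be eligible, the share agreeing is thus close to 100% by construction; among all truly eligible patients, it is unknown.

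The analysis section then divides by invited patients instead and keeps the same ±6%. The two ratios coincide only if every invited patient would score at least 20, in which case the screen would have no purpose.

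The trial exists to inform a larger one. Read as a rate per patient approached, 20% means five approaches per randomised participant. If some consenters fail the PHQ-ADS, more are needed. This trial could also fall short of 40 with consent running exactly to plan, and the shortfall could be mistaken for unwillingness when it came from screen failure.

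**Working it through.** **Inputs from the Sample size section:** target rate p = 0.20, n = 200 eligible patients, 40 to be recruited, ±6% at 95% confidence. The documents give no PHQ-ADS pass rate; 30% to 70% is assumed throughout.

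**1. The plan's own figure.** The Wald half-width is 1.96 × √(p(1 − p)/n) = 1.96 × √(0.2 × 0.8/200) = 0.0554, or 5.5 points. The Wilson interval for 40/200 is 15.0% to 26.1% and the exact interval 14.7% to 26.2%. The stated ±6% is reproduced after rounding. The arithmetic is sound.

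**2. Enrolled/eligible is not identified.** As an illustration, suppose 200 are invited, 40 enrolled and 160 never scored. If a share u of those 160 would score at least 20, the rate among eligible patients is 40/(40 + 160u):

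| u (assumed) | Eligible | Rate |
|---|---|---|
| 0.3 | 88 | 45% |
| 0.5 | 120 | 33% |
| 0.7 | 152 | 26% |
| 1.0 | 200 | 20% |

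The same observed counts fit every row. The 20% appears only if all 160 are eligible.

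**3. If eligible means eligible before screening.** Then 200 patients at 20% give 40 consenters. With pass rate r among consenters, the number randomised is 40r:

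| r (assumed) | Randomised | Of 200 invited | Wald half-width |
|---|---|---|---|
| 0.3 | 12 | 6% | 3.3 points |
| 0.5 | 20 | 10% | 4.2 points |
| 0.7 | 28 | 14% | 4.8 points |
| 1.0 | 40 | 20% | 5.5 points |

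To randomise 40 at 20% consent, 40/(0.2r) must be invited: 667, 400 or 286 for r = 0.3, 0.5 or 0.7. That is about 17, 10 or 7 invitations per randomised participant, against 5 if nobody fails the screen.

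**4. If 200 truly score at least 20.** Let s be the share of invited patients who score at least 20. This is a different quantity from r, because consent may depend on symptoms. Invited = 200/s, which is 667, 400 or 286 for s = 0.3, 0.5 or 0.7. Forty enrolled is then 6%, 10% or 14% of those invited, with half-widths of 1.8, 2.9 and 4.0 points.

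**5. Does ±6 points survive the change of denominator?** At n = 200 the half-width reaches 6 points when p(1 − p) = 200 × (0.06/1.96)² = 0.187, so p is about 25%. For any rate below that, and for larger n at the same rate, it is smaller. Every half-width in steps 3 and 4 lies inside ±6.

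**The case against.** The analysis section already specifies ratios with observable denominators: agreeing to screening out of invited, and enrolled out of invited. The co-primary outcomes are counts that need no eligible denominator. A reader might therefore infer from the PHQ-ADS timing that recruitment cannot be estimated at all. The documents do not support that; only the quantities defined on eligible patients are affected.

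A reader might also infer that ±6% is wrong once the denominator becomes invited. It is not: the Sample size section says within ±6%, and step 5 shows the bound holding in every scenario considered. The Quantitative data section does not repeat the 20%, so it does not claim 20% ± 6% of those invited.

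The word eligible may simply mean potentially eligible before screening, a sense the Quantitative data section uses elsewhere. Fig. 1 is not shown, so a pre-screen in the flow diagram cannot be ruled out, although the Screening and enrolment text places the PHQ-ADS after consent. Finally, analyses are descriptive and no decision rule rests on the 20%.

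These points limit the seriousness but do not remove the problem. On the pre-screen reading the rate is estimable, yet the step from 20% of 200 to 40 randomised still assumes that no consenter fails the PHQ-ADS. On the literal reading, a stated indicator and a stated target cannot be calculated. A later analysis plan cannot recover scores that were not collected.

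**Conclusion.** The point holds as a conflict of definitions. The 20% target and the indicator based on eligible patients cannot be calculated as written, because PHQ-ADS status is unknown for everyone who does not consent. The analysed ratio, enrolled over invited, can be calculated, and its half-width would probably stay within ±6 points. What does not carry over is the 20% target and the expectation of 40 from 200.

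On the pre-screen reading, 40 consenters give 12 to 28 randomised, or 6% to 14% of 200 invited. That range follows entirely from the assumed 30% to 70% pass rate, which nothing in the documents anchors. The inconsistency itself needs only that some patients score below 20.

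This should be fixed. It does not invalidate the trial, since the counts needed for a correct rate are already planned.

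**What to change.** 1. Choose one observable denominator, either all invited patients or patients eligible on every criterion except the PHQ-ADS, and use it in Feasibility outcomes, Sample size and Quantitative data.
2. Report three steps: consented/invited, PHQ-ADS ≥20/consented, and randomised/invited. Give each a 95% interval computed from the observed counts (Wilson or exact), and delete the fixed ±6% from Quantitative data.
3. In Sample size, restate the 20% target, the expected 40 and the precision for the chosen denominator, with an explicit assumption for the PHQ-ADS pass rate. If 20% is meant as a consent rate, say so and show how many invitations 40 randomised participants then require.

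The cost is wording. The counts of patients invited, screened, excluded and enrolled are already to be recorded; the PHQ-ADS pass rate comes from the same screening log. The downside is a less favourable stated target: a lower randomised share per patient invited, or more patients to invite within the 3 months.
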